### 3.8.2 Sample size for the immunogenicity section

Various options for the calculation of the sample size needed for the immunogenicity section were analyzed. Various laboratory tests (cLia, total IgG, neutralizing antibodies, etc.) were performed during previous studies on the topic, resulting in an important heterogeneity in seropositivity levels and antibody titers reported after 2 or 3 doses of Gardasil®(32,34,35).

Taking into consideration that there is no « gold standard » for the laboratory tests measuring antibodies against HPV and that the sensitivity of the tests currently used varies significantly from one test to another, it was decided not to base the sample size calculation on seropositivity. We have assumed appropriate to base our sample size calculation on the ratio of geometric mean titers (GMT) expected in the 2 study groups (GMT2/GMT3).

The lower limit of the GMT ratio's confidence interval was set at 0.5, given that it is generally the case in this type of study(85,86). Because of potential clinical impacts, and future public health decisions, we want to have enough statistical power to detect a ratio  $\geq 0.65$  between the groups. To demonstrate a ratio of 0.65 between GMT2/GMT3 with a lower limit higher than 0.5, a statistical power of 90% and a significance level of 5%; the sample size needed is a total of 138 participants assessed per group at the end of the study (Table 2).

Taking into consideration a full respect of the study protocol (per-protocol) of 80 to 90% and a loss to follow up of about 5% per year, the enrolment of 500 participants (250 per group) was deemed necessary to be able to establish non-inferiority between the two study groups with a statistical power  $\geq 90\%$  ( $\alpha = 5\%$ ). The enrolment of 500 participants at the beginning of the study (month 60 post primary immunization) will enable us to have at least 138 participants assessed at the end of the study.

Table 2. GMT2/GMT3 ratio: non-inferiority test with a lower limit set at 0.5

| Lower limit | Ratio | N per group |
|-------------|-------|-------------|
| 0.5         | 0.55  | 1034        |
| 0.5         | 0.6   | 284         |
| 0.5         | 0.65  | 138         |
| 0.5         | 0.7   | 84          |

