### 3.9 Analysis

Descriptive analyses will be used to describe the participants and compare the two study groups. Specifically, the following analyses will be performed for each of the objectives mentioned in section 2.

For the primary objective:

A survival analysis (time to event analysis) will be performed in order to answer the main study questions. This approach will take into consideration the different duration of follow-up resulting from the fact that the date of entry in the cohort will vary between participants. Time 0 will be defined as the date of randomization. The time of event will be defined as the first occurrence of a persistent infection. Participants with no persistent infection will be censored (right-censored) at: (a) loss to follow-up, (b) death or (c) end of the study whichever comes first. The preliminary analyses will include the comparison of the Kaplan-Meier curves using a non-parametric test (*log-rank test*, *Wilcoxon*) describing how the proportion of participants developing a persistent infection varies over time in each group. The main non-inferiority analysis will rely on the Hazard ratio's (HR) 95% confidence interval. Adjusted analyses will take into consideration the potential confounding factors collected with the annual questionnaire. If the HR's upper limit is not higher than 1.05 (representing a 5% difference of efficacy between the two schedules), we will conclude to a non-inferiority of the 2-dose calendar.

This analysis will then be repeated with the « intention-to-treat » method to evaluate the differences generated by a change in the exposure's definition. Sensitivity analyses will also be performed to evaluate the impact of modifying the outcome's definition. Indeed, it is likely that some girls will not exactly respect the vaginal self-samplings' schedule. We will vary the primary outcome's definition (e.g. consider as persistent infection only if the sample were consecutive and 6 months apart, or

consider as persistent infection a situation where the same type of virus was identified in two consecutive samples regardless of the number of months between the samples).

For the secondary objectives on immunogenicity (objectives 2.2.a and c), two analyses will be performed to measure non-inferiority at month 120:

1) An intention-to-treat analysis (*ITT analysis*) in which all the serologic results available will be included.

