2) A per protocol (*according to the protocol, ATP analysis*) which will only include the participants who respected all the procedures planned in the protocol related to the immunogenicity analysis.

All the statistical tests will be performed with a type I error set at 5%. Percentages of seropositivity will be compared with a Chi square or Fisher test. GMTs will be compared with a *t*-test.

Among seropositive samples, GMTs will be calculated for each of the 3 time points planned in the protocol. GMTs obtained in the two groups at different study points will be compared using an analysis of variance (ANOVA) and a Duncan's multiple range test performed with SAS version 9.1.

For the other secondary objective on condylomas (2.2.d), we will mainly perform descriptive analyses as described at the beginning of this section.

An exact poisson regression is planned at the end of the study to compare the persistent infections observed among the vaccinated girls of the two study groups to that of an historical cohort of unvaccinated girls. Therefore, we will be able to calculate the number of persistent infections prevented by vaccination i.e. the difference between the expected and observed number of persistent infections (2.2.e).

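### Section 3.9 sets a non-inferiority aim for antibodies at month 120 but names tests that are ordinarily tests of equality and do not apply the 0.5 GMT-ratio limit of section 3.8.2

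*Protocol*

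**What the plan says.** Section 3.9 introduces the month-120 immunogenicity work for objectives 2.2.a and 2.2.c by stating that "two analyses will be performed to measure non-inferiority at month 120", one by intention to treat and one per protocol. The methods follow, all at a 5% type I error. For seropositivity the text reads "Percentages of seropositivity will be compared with a Chi square or Fisher test"; for titres it reads "GMTs will be compared with a" t-test. An ANOVA with Duncan's test is added for the study time points. For immunogenicity, section 3.9 gives no ratio, confidence interval, margin or shifted null value.

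The non-inferiority criterion is in section 3.8.2: "The lower limit of the GMT ratio's confidence interval was set at 0.5". The sub-study is sized "To demonstrate a ratio of 0.65 between GMT2/GMT3 with a lower limit higher than 0.5", with "a statistical power of 90% and a significance level of 5"%, and "the sample size needed is a total of 138 participants assessed per group at the end of the study". The same section explains that seropositivity was not used for sizing, because assays differ in sensitivity and none is a reference standard. The protocol gives no non-inferiority limit for seropositivity.

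**The concern.** A non-inferiority conclusion needs a margin and an interval, or a test whose null value is the margin. A t-test or chi-square test in its usual form asks whether the groups differ at all. A significant result does not refute non-inferiority, and a non-significant one does not establish it. For the primary objective, section 3.9 supplies a hazard-ratio interval, a numerical limit and a decision rule. For the month-120 antibody objectives it supplies named tests only and does not refer back to 3.8.2.

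An analyst who follows 3.9 alone would therefore report a p-value for equality under a non-inferiority aim. For GMTs, that p-value will almost always be significant in the scenario the sub-study was sized for. For seropositivity, a non-significant result could be read as non-inferior although no acceptable loss was ever defined. Seropositivity also matters because section 3.9 calculates GMTs among seropositive samples, so participants who have lost detectable antibody show up only in the seropositivity comparison.

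**Working it through.** **Inputs.** From 3.8.2: limit 0.5, planning ratio 0.65, power 90%, significance level 5% (sidedness not stated), 138 per group at the end of the study, and table rows of 1034, 284, 138 and 84 for true ratios 0.55, 0.60, 0.65 and 0.70. The SD of ln titre is not given and is back-solved. The seropositivity rates are assumptions.

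**1. Reproducing 138.** On the ln scale, n per group = 2 × SD² × (z for alpha + z for power)² / [ln(ratio/0.5)]², with ln(0.65/0.5) = 0.2624.
- One-sided 2.5%, SD 0.67: 2 × 0.4489 × (1.960 + 1.282)² / 0.0688 ≈ 137.1, rounded up to 138. The exact noncentral-t calculation with SD 0.668 gives 1034, 284, 138 and 84, which are all four rows.
- One-sided 5%, SD 0.74: 1034, 283, 137 and 84, which fits almost as well.

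One common SD fits the whole table, so the design test was a GMT-ratio test against 0.5. The alpha behind it cannot be settled from the table.

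**2. Two procedures on the same planning scenario (true ratio 0.65, 138 per group).** SE = SD × √(2/138). Probability of meeting the 0.5 rule = Φ(0.2624/SE − z). Probability that a two-sided 5% equality test is significant ≈ Φ(0.4308/SE − 1.96), since |ln 0.65| = 0.4308.

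| | SD 0.668 | SD 0.74 |
|---|---|---|
| SE | 0.0804 | 0.0891 |
| 0.5 rule met, alpha used in sizing | 90% (z = 1.96) | 90% (z = 1.645) |
| 0.5 rule met, two-sided 95% CI | 90% | 84% |
| Equality t-test significant | over 99.9% | 99.8% |
| 95% CI at an observed ratio of 0.65 | 0.555 to 0.761 | 0.545 to 0.775 |

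**3. Range of observed ratios affected.** With a two-sided 95% CI (t quantile 1.969), the 0.5 rule is met when the observed ratio exceeds 0.5 × exp(1.969 × SE), which is 0.59 (SD 0.668) or 0.60 (SD 0.74). The equality test is significant when the ratio is below exp(−1.969 × SE), which is 0.85 or 0.84. Any observed ratio in between is within the margin and also significantly lower. At a true ratio of 0.80, the 0.5 rule is met in over 99.9% of trials, and the equality test is still significant in 79% or 70%. The reverse case, non-significant but failing the 0.5 rule, does not arise for a lower GMT at 138 per group, because a non-significant ratio is above 0.84.

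**4. Seropositivity.** The table shows the probability that a two-sided Fisher test is non-significant, by full enumeration. 138 is the required minimum. 250 enrolled with 5% yearly loss over five years leaves 250 × 0.95⁵ ≈ 193.4, taken as 194.

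| Assumed rates, 3 doses v 2 doses | 138 per group | 194 per group |
|---|---|---|
| 99% v 94% | 49% | 28% |
| 98% v 93% | 60% | 41% |
| 95% v 90% | 73% | 61% |

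One illustrative result: 134/138 v 128/138 gives Fisher p = 0.17, while the Newcombe 95% CI for the difference runs from −10.2 to +1.1 points. The non-significant test does not exclude a 10-point loss.

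**The case against.** The 0.5 criterion is in the protocol, and 3.9 offers no competing rule. Nowhere does the protocol say that non-inferiority follows from a non-significant test or is refused on a significant one. Interval construction and decision wording for a secondary endpoint are commonly left to an analysis plan. The null value of the t-test is not stated, and a t-test on log titres against ln 0.5 would be exactly the 3.8.2 rule. Objectives 2.2.a and 2.2.c speak only of comparing, which the named tests suit. Section 3.8.2 deliberately set seropositivity aside for sizing.

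Much of this stands and limits the point. A reader might infer that the plan contradicts itself or yields opposite verdicts on GMTs. It does not: a titre can be significantly lower and still within the margin. A reader might also infer that a real seropositivity loss would usually be missed. The figures do not support that: at 138 per group one of the three assumed scenarios gives 49%, and at 194 two of the three fall below half.

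What does not stand is the view that this is only detail left for later. Section 3.9 names its methods, states non-inferiority as their purpose, and mentions neither the margin nor 3.8.2. The charitable reading of the t-test has to be supplied by the reader, and for seropositivity there is no rule elsewhere to supply.

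**Conclusion.** The point holds as a mismatch between stated aim and named method. Read in the ordinary way, the tests in 3.9 do not apply the criterion in 3.8.2. In the planning scenario the 0.5 rule is met in about 90% of trials, while an equality t-test is significant in about 99.8% or more, so the t-test cannot be the non-inferiority verdict. Misusing it that way would err towards denying non-inferiority of GMTs, not towards claiming it falsely. For seropositivity, a non-significant Fisher test would not exclude a loss of about 5 points.

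The GMT figures rest on a back-solved SD of 0.67 to 0.74, and the conclusion is the same across that range. The seropositivity figures rest on assumed rates. The sample size of 138 is reproduced and is not in question. This concerns secondary objectives and does not touch the primary outcome.

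**What to change.** In 3.9, state that month-120 non-inferiority of GMTs is concluded when the lower limit of the two-sided 95% confidence interval of GMT2/GMT3, computed from log titres, exceeds 0.5. Keep the t-test only as a supplementary comparison. Confirm at the same time that 138 per group was sized at one-sided 2.5%. If it was one-sided 5%, the two-sided 95% interval has about 84% power at 138 per group rather than 90%, and that should be disclosed.

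Report seropositivity as a difference in proportions with a 95% confidence interval, label it descriptive, and state that no non-inferiority is inferred from a non-significant test.

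The cost is wording in the protocol or analysis plan, with no new data. Seropositivity loses the appearance of a formal test, and the possible loss of GMT power applies only under the one-sided 5% reading.

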### **3.3 Enrolment**

After approval by the Commission d'Accès à l'Information we will contact the Quebec health insurance board (Régie de l'Assurance Maladie du Québec, RAMQ) in order to obtain the contact information of girls aged 9 years on September 30th, 2008 (i.e. born between October 1st, 1998 and September 30th, 1999 for the first enrolment year), 9 years on September 30th, 2009 (i.e. born between October 1st, 1999 and September 30th, 2000 for the second enrolment year), 9 years on September 30th, 2010 (i.e. born between October 1st, 2000 and September 30th, 2001 for the third enrolment year), 9 years on September 30th, 2011 (i.e. born between October 1st, 2001 and September 30th, 2002 for the fourth enrolment year).

From September 2013 to June 2014 we will contact the girls' parents by mail to invite those who received 2 doses of Gardasil® during the 2008-2009 academic year. The letter will explain the purpose of the project, how it will be carried out and details on inclusion criteria. This same step will be carried out in 2014, 2015 and 2016.

A phone number and an e-mail address will enable parents to contact a research nurse (1) to obtain further information, (2) to check eligibility and (3) to take an appointment with a research nurse at the coordinating center.

During this appointment, the research nurse will confirm the participant's eligibility, will obtain informed consent from the girl and her parent, will perform a urine pregnancy test on the girl and will randomize her to one of the groups, administer the 3rd dose if she was assigned to the «3rd dose» group and collect the blood sample if she is part of the subgroup targeted by the secondary objective on immunogenicity. A financial compensation will be offered to the girl and parent 20,00\$ each) for this face-to-face appointment. The participant will collect the first HPV vaginal sample after receiving explanations on the self-sampling procedure and will fill the first questionnaire. A financial compensation will be provided for each self-sampling kit received (5,00\$ per sampling, then 10,00\$ per sampling when the girl turns 18 years of age).

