### **3.5.3 Secondary outcomes: definition and measurement**

#### **a) Immunogenicity:**

A sub-sample of girls will be assigned to the part of the study measuring the immunogenicity and comparing seropositivity and antibody geometric mean titers (for HPV types 6, 11, 16, 18) in the two study groups.

The first 500 participants recruited will participate to the immunogenicity section of the study (250 per group). A blood sample will be collected at month 60, 90 and 120 following the beginning of vaccination in these participants. Five milliliters of blood will be collected in an 8.5 ml marbled-tube. Only 350 participants will have a blood sample at month 90.

A non-competitive serologic Luminex platform developed by the Quebec public health laboratory (Laboratoire de santé publique du Québec, LSPQ) will be used to detect and quantify HPV types' specific antibodies. This test is sensitive, replicable and quite simple to use(76,77). Depending of

the availability of the LSPQ Luminex platform, laboratory assays could be performed at the Centers for Disease Control and Prevention (CDC, Atlanta, USA) using multiplex direct IgG ELISA to HPV L1+L2 virus-like particles (VLPs) on Meso Scale Discovery platform as previously described with minor modification(78).

Clinical samples from the Vaccine Research Team CHU de Québec-Université Laval biobank (Nagano project #B12-06-986) will be used by the Frederick National Laboratory for Cancer Research (NIH/CDC) for the "9v HPV seronegatives to harmonize threshold" project to develop and validate HPV serological tests.

b) Primary outcome up to 13 years

HPV-16 and HPV-18 infections that persist at least 6 months will be measured, and this, up to **13 years** following the first injection as defined in 3.5.2.

c) Immunogenicity for 5 other types:

A sub-sample of girls will be assigned to the part of the study measuring the immunogenicity and comparing seropositivity and antibody geometric mean titers (for HPV types 6, 11, 16, 18 **and 31, 33, 45, 52, 58**) in the two study groups.

d) Condylomas:

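### The GMT comparisons do not use the month-60 titre taken at the randomisation visit; adjusting for it would tighten the month-120 GMT ratio at almost no cost

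*Protocol*

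**What the plan says.** Section 3.9 names the tests for the immunogenicity objectives: "Percentages of seropositivity will be compared with a Chi square or Fisher test. GMTs will be compared with a" t-test. The next paragraph adds a second method: "GMTs obtained in the two groups at different study points will be compared using an analysis of variance (ANOVA") with Duncan's multiple range test. Neither sentence names a covariate. The only adjusted analyses in section 3.9 belong to the primary hazard ratio and draw on the annual questionnaire.

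The decision on titres is tied to one visit: "two analyses will be performed to measure non-inferiority at month 120", once by intention to treat with all available serology and once per protocol. Section 3.8.2 sets the limit for the ratio GMT2/GMT3 at 0.5.

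A baseline titre is planned for the whole subgroup. Section 3.5.3 a) says "The first 500 participants recruited will participate to the immunogenicity section of the study (250 per group"), and then "A blood sample will be collected at month 60, 90 and 120 following the beginning of vaccination in these participants". Only the month-90 draw is cut back, to 350 girls. Section 3.8.2 equates month 60 with study entry. Section 3.3 places the draw at the appointment where the girl is randomised and, if so allocated, vaccinated; the nurse is to "collect the blood sample if she is part of the subgroup targeted by the secondary objective on immunogenicity".

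**The concern.** A girl's month-60 titre for a given HPV type is a natural predictor of her later titre for that type. It is measured at randomisation, before a third dose can show in the serum. Section 3.3 mentions the draw after the dose, but both happen at one visit, and section 1.4 puts the antibody peak a month after vaccination.

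An unadjusted comparison leaves stable differences between girls in the error term. It also lets the predictive part of any chance difference in month-60 titres carry into the later ratio. The month-120 ratio is the non-inferiority test for objectives 2.2.a and 2.2.c, so the width of its interval decides whether the lower limit clears 0.5. Both objectives already require the month-60 assays, so the covariate needs no extra blood or laboratory work.

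**Working it through.** **Inputs from the protocol.** Limit 0.5, planned ratio 0.65, 90% power, 5% significance, 138 per group (3.8.2). The table there also gives 1034, 284 and 84 per group for ratios 0.55, 0.60 and 0.70. Enrolment is 250 per group, 80 to 90% per protocol, about 5% loss per year (3.8.2).

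**Inputs that are not in the protocol.** The SD of ln titre was solved from the table. The correlation rho is assumed.

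**Reproducing the table.** Take a two-sample non-inferiority test on ln titre, distance ln(ratio/0.5), one-sided 0.025. A noncentral-t calculation with a coefficient of variation of 0.75, that is SD = sqrt(ln(1 + 0.75²)) = 0.668, returns exactly 1034, 284, 138 and 84. A one-sided 0.05 reading with SD about 0.74 also fits. The SD is therefore an inference, but the percentage gains in interval width below do not depend on it. No baseline adjustment is needed to fit the table.

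**Effect of adjustment.** Error variance is multiplied by 1 − rho², and interval width on the log scale by sqrt(1 − rho²).

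- Unadjusted SE of the ln ratio at 138 per group: 0.668 × sqrt(2/138) = 0.0804.
- Power at ratio 0.60: Φ(ln 1.2 / SE − 1.96). With rho = 0: 0.1823/0.0804 − 1.96 = 0.31, so 62%.
- Power at ratio 0.65: Φ(ln 1.3 / SE − 1.96). This row uses SD 0.672, the normal-approximation value that returns 90.0% at 138 per group.

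| rho (assumed) | 1 − rho² | CI narrower by | 138 per group acts like | Power at 0.65 | Power at 0.60 |
|---|---|---|---|---|---|
| 0 (t-test) | 1 | 0 | 138 | 90.0% | 62% |
| 0.3 | 0.91 | 5% | 152 | 92.5% | 66% |
| 0.5 | 0.75 | 13% | 184 | 96.3% | 74% |
| 0.7 | 0.51 | 29% | 271 | 99.5% | 89% |

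**Unequal correlation.** The third dose may loosen the link with the earlier titre in that arm. With rho 0.8 in the 2-dose arm, 0.3 in the 3-dose arm and equal SDs, the average governs: (0.8 + 0.3)/2 = 0.55, and 1 − 0.55² = 0.70. The interval narrows by about 16%.

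**Numbers the design expects to keep.** 250 × 0.80 × 0.95⁵ = 155 and 250 × 0.90 × 0.95⁵ = 174 per group. At ratio 0.65 the t-test then has about 93 to 95% power. At 0.60 it has about 67 to 72%, against 79 to 84% with rho 0.5 and 92 to 95% with rho 0.7.

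**The 0.60 row.** The protocol's table asks for 284 per group here, more than the 250 enrolled. With adjustment the requirement is about 284 × 0.75 = 213 at rho 0.5, or 284 × 0.51 = 145 at rho 0.7. Only the latter falls within the 155 to 174 expected.

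**The case against.** The strongest reply is that nothing here is wrong. A t-test on log titres is valid under randomisation, and its interval already allows for chance imbalance at month 60. That stands. A reader might infer that the planned comparison is biased; the documents do not support this.

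A reader might also infer that the objective is underpowered. At the planned ratio of 0.65 it is not. The design needs 138 per group and expects to keep 155 to 174, and section 3.4 reports fewer losses than expected. The larger power gains arise at 0.60, a row of the protocol's table but not its planning target.

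The size of the gain is also open. The protocol gives no correlation, so one high value applied to both arms and all types would overstate the case. The boosted arm may correlate less. Section 1.2 shows that types 31, 33, 45, 52 and 58 are not in the quadrivalent vaccine, so their month-60 titres may be low and predict little. Girls below the cut-off at month 60 need a rule, or adjustment would drop them from an intention-to-treat set meant to hold all available results.

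It may finally be said that model detail belongs in the statistical analysis plan. But the protocol names its methods, and as named they leave the baseline out.

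**Conclusion.** The point holds as a loss of precision in a secondary non-inferiority analysis. Across assumed correlations of 0.3 to 0.7 the interval for GMT2/GMT3 would be about 5 to 29% narrower, and about 16% narrower in the mixed case of 0.8 and 0.3. At the planned ratio this adds a margin to power that is already adequate. If the true ratio is nearer 0.60, it could decide whether non-inferiority is shown.

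The power figures rest on an SD of about 0.67 solved from the protocol's table, and all the gains rest on an assumed rho. If rho is small, almost nothing is gained and almost nothing is lost.

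Adjustment does not address a separate feature of section 3.9: "Among seropositive samples, GMTs will be calculated for each of the 3 time points planned in the protocol". That selection is made after randomisation, and a baseline covariate does not cure it.

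**What to change.** Make the month-120 non-inferiority analysis, for each HPV type, an analysis of covariance of log titre on randomised group, that type's month-60 log titre and centre (the randomisation stratum in section 3.6), allowing unequal variances between groups. Back-transform the adjusted difference to GMT2/GMT3 and read its 95% CI against 0.5. Use the same model for the month-90 comparison, which carries no non-inferiority decision.

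Give month-60 results below the assay cut-off a fixed value, for example half the cut-off, with an indicator in the model, so that no girl leaves the intention-to-treat set. Keep the unadjusted ratio as a sensitivity check. Fix the model before anyone sees unblinded titres.

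The cost is a few sentences in section 3.9 or the statistical analysis plan. No further sampling or assays are needed.

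### The only stated rule for GMTs uses seropositive samples; if it governs the month-120 ratio, a 2-dose deficit is understated and non-inferiority is favoured

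*Protocol*

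**What the plan says.** Section 3.9 announces, for objectives 2.2.a and 2.2.c, that "two analyses will be performed to measure non-inferiority at month 120". The first is an intention-to-treat analysis "in which all the serologic results available will be included"; the second is restricted to participants who followed the procedures. Seropositivity is to be compared by chi-square or Fisher test and GMTs by t-test. The next paragraph reads "Among seropositive samples, GMTs will be calculated for each of the 3 time points planned in the protocol", followed by ANOVA and Duncan's test across study points.

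The three time points come from section 3.5.3: "A blood sample will be collected at month 60, 90 and 120 following the beginning of vaccination in these participants". Section 3.8.2 supplies the criterion that sizes this part of the trial: "The lower limit of the GMT ratio's confidence interval was set at 0.5".

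The protocol gives no titre value for a seronegative sample, no expected seropositivity and no standard deviation of log titre.

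**The concern.** The month-60 sample is taken at the randomisation visit, so seropositivity there is a baseline characteristic. At months 90 and 120 it is an outcome that the third dose can change. A GMT among seropositives at month 120 therefore compares two selected subsets, not the randomised groups.

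The direction of the selection matters. Section 1.4 expects a booster at five years to raise titres, and section 3.8.2 plans for a ratio of 0.65, so the protocol itself anticipates lower titres in the 2-dose group. With one cut-off for both groups, more low values are then removed from the 2-dose group. Its GMT rises more than that of the 3-dose group, and the ratio moves up, away from the 0.5 limit. At stake is the error rate of the one immunogenicity conclusion for which a sample size was calculated.

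**Working it through.** **Inputs from the protocol.** Section 3.8.2: limit 0.5; assumed true ratio 0.65; 90% power at the 5% level; 138 assessed per group; per-protocol adherence of 80 to 90%; loss of about 5% per year; 250 enrolled per group.

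**Inputs assumed.** Log-normal titres, equal spread, one cut-off for both groups, and the seronegative fraction, which is varied.

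**Step 1: the plan's own figure.** The SD is not stated, so 138 cannot be derived from stated inputs alone, but it can be back-solved. With one-sided 0.025 and 90% power, (1.960 + 1.282)² = 10.507 and n = 2 × 10.507 × s² / [ln(0.65/0.5)]². Setting n = 138 with ln 1.3 = 0.2624 gives s = 0.672. A t-based calculation with s = 0.668 returns all four rows of the section 3.8.2 table exactly (1034, 284, 138, 84). The table is internally consistent. If the 5% was meant as one-sided, s is about 0.74.

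**Step 2: number assessed.** 250 × 0.80 × 0.95⁵ = 154.8, so 155 per group at the lower end of the stated adherence.

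**Step 3: shift of the ratio.** For a group with log mean μ and cut-off c, the seropositive-only mean is μ + s·φ(a)/[1 − Φ(a)], with a = (c − μ)/s. Take a true ratio of 0.50 and 10% seronegative in the 2-dose group:
- 2-dose: a = −1.282; shift = 0.672 × 0.1755/0.900 = 0.131.
- 3-dose: a = −1.282 − 0.693/0.672 = −2.313 (about 1% seronegative); shift = 0.672 × 0.0275/0.990 = 0.019.
- Ratio = exp(−0.693 + 0.131 − 0.019) = 0.56.

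**Step 4: false non-inferiority.** Simulation of 20,000 trials, true ratio exactly 0.50, 155 per group, s = 0.672; non-inferiority is declared if the lower limit of the two-sided 95% t interval exceeds 0.5:

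| Seronegative, 2-dose | Seronegative, 3-dose | Seropositive-only ratio | Declared non-inferior, seropositive only | All samples |
|---|---|---|---|---|
| 1% | under 0.1% | 0.51 | 4% | about 2.5% |
| 5% | 0.4% | 0.53 | 14% | about 2.5% |
| 10% | 1% | 0.56 | 33% | about 2.5% |
| 20% | 3% | 0.60 | 76% | about 2.5% |
| 27% | 5% | 0.63 | 91% | about 2.5% |

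The percentages are rounded, and small changes in the seronegative fraction move the entries by a point or two.

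**Step 5: sensitivity to the SD.** At 138 per group, 5% seronegative in the 2-dose group gives 12.8%, 12.5% and 10.6% false non-inferiority for s = 0.67, 0.74 and 1.0; 10% seronegative gives 31%, 29% and 23%. The finding does not hinge on the back-solved SD.

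**The case against.** **The sentence may not govern the non-inferiority test.** It opens a new paragraph and leads into the ANOVA across study points, so it could be meant for the time course only. A reader might infer that the protocol definitely fixes a seropositive-only ratio for the month-120 test; no sentence says so. What remains is that month 120 is one of the three time points and that no other rule for calculating GMTs is given.

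**A reader might call the two sentences a flat contradiction.** That goes too far. The intention-to-treat and per-protocol labels describe which participants or results enter, and the seropositivity comparison uses every result in any case. A set definition and a computing rule can coexist. The protocol does not say how they fit together here.

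**The effect may be small.** The protocol describes the vaccines as very immunogenic and gives no seronegative rate. With 1% or 2% seronegative in the 2-dose group the false-positive rate is about 4% or 6%. This stands, and it is why the whole range is shown.

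**The selection would be visible.** Seropositivity is compared separately. Fisher's test at 155 per group is significant in 94% of trials at 1% versus 10% seronegative and in 99.9% at 3% versus 20%. The larger deficits would thus usually be flagged, but the flag does not correct the ratio or its interval.

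**A reader might infer that the distortion is worst under "Immunogenicity for 5 other types".** The documents do not support this. The third dose is Gardasil, which contains none of those types. No passage gives their seropositivity or predicts a 2-dose deficit for them, and with a ratio near 1 the truncation causes little bias.

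**Conclusion.** The concern holds in conditional form. The protocol's only GMT rule is restricted to seropositive samples and is not reconciled with the all-results intention-to-treat analysis. If the month-120 ratio follows that rule, it is biased towards 1, and with lower 2-dose titres towards non-inferiority. The effect is negligible near 100% seropositivity, noticeable at 95% in the 2-dose group (about 14% false non-inferiority instead of 2.5%) and serious at 90% or below (33% and more).

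These figures rest on log-normal titres, equal spread, a common cut-off, an SD back-solved from 138 per group and assumed seronegative rates. A ratio above 1 or unequal spread could change the direction. The rates are scenarios, not a forecast that the trial will reach a wrong conclusion. The objective is secondary, so this should be corrected but does not touch the primary result.

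**What to change.** State in section 3.9 that the month-120 GMT ratio and its confidence interval are computed on all available samples in the intention-to-treat and per-protocol sets. Keep measured titres that fall below the seropositivity cut-off at their measured value. Treat only results below the assay's quantification limit as left-censored in a censored-normal model, with a fixed substitution value as sensitivity analysis. Report seropositive-only GMTs as descriptive.

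Setting every seronegative result to half the cut-off should not be the main method. It discards measured values, and at the design ratio of 0.65 it lowers power from about 93% to 87%, 82% and 78% with 1%, 3% and 5% seronegative in the 3-dose group.

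The cost is a few sentences, slightly more analysis work and a less favourable ratio. No new samples are needed.
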